## Abstract

Online advertising is an important tool that can be utilized by charities to elicit attention and funding. A critical examination of advertisement strategies is thus necessary to increase the efficacy of fundraising efforts. Previous studies have shown that individuals’ moral views and perceptions of social norms can play important roles in charitable behavior. Thus, the current protocol describes a study to examine whether framing charitable advertisements in line with participants’ morality and increasing the salience of descriptive social norms increases subsequent charitable behavior. We describe experimental, online methods, whereby participants are provided with a framed call-to-action and normative information within a custom-developed application or existing survey platform. Furthermore, in the exploratory fashion, we discuss the possibility of collecting participants’ Facebook data and predicting moral profiles from this data. If there is an increased rate of donations as a result of moral compatibility and/or increased norm salience, charities can leverage this knowledge to increase the donations by tailoring their campaigns in a more appealing way for their prospective donors. Moreover, if it turns out to be possible to predict one’s moral profile from Facebook footprints, charities can use this knowledge to find and target people that are more likely to support their cause. However, this introduces important ethical questions that are discussed within this protocol.

## Introduction

Charities often provide a vital service for marginalized and vulnerable people in society. Given that individual charitable giving now contributes the largest proportion of income for all registered charities in the United Kingdom (The National Council for Voluntary Organisations [NCVO], 2017), it is vital that charities maximize the effectiveness of their campaigns. A promising avenue for increasing the efficiency of charitable fundraising with little or no additional cost are campaigns in the digital sphere, a rapidly growing platform for philanthropy. In various reports, MacLaughlin (2012, 2014, 2017) has shown that online giving has been steadily growing in past years. For example, between 2013 and 2014, it increased by 8.9% (MacLaughlin, 2014). Furthermore, from 2015 to 2016, online giving increased by 2.8% in the United Kingdom and 7.9% in the United States (MacLaughlin, 2017). The following protocol suggests a method to study whether tailored appeals and salient social norms can be utilized to increase individual charitable behavior. The findings based on this protocol could significantly aid the online marketing strategies of charitable organizations.

### The Determinants of Charitable Behavior

In this protocol, charitable behavior (CB) refers to the measurable actions of supporting a charity through donating money or time. To construct an intervention that influences CB, it is first necessary to identify its potential determinants. CB has often been examined in the context of the Theory of Planned Behavior (TPB; Ajzen, 1985, 1991). In the TPB, the immediate causes of any behavior are (1) intentions to perform that behavior and (2) the actual control one has over performing it. In turn, behavioral intentions result from individuals’ attitudes, social norms and perceived behavioral control. Indeed, some studies found that these TPB variables are good predictors of CB. For example, van der Linden (2011) found that attitudes, perceived behavioral control, past behavior and moral norms significantly predicted charitable giving intentions. Smith and McSweeney (2007) reported similar results, but identified injunctive norms as an additional predictor of charitable giving intentions. Thus, one way to increase CB is to influence one or more of its immediate causes, such as changing attitudes and referencing a social norm.

#### Changing Behavior by Changing Attitudes

An intervention aimed at increasing CB may focus on changing people’s attitudes toward CB. One promising way of doing this is by using the assumptions of Regulatory Fit Theory (Higgins, 2005). According to Regulatory Fit Theory (RFT), it is possible to increase the effectiveness of a persuasive appeal by framing the arguments of a persuasive message in a way that fits one’s psychological characteristics. This could include motivational orientation (Updegraff et al., 2007), personality (Hirsh et al., 2012) or moral characteristics (Feinberg and Willer, 2013). Regulatory fit is hypothesized to shift attitudes through three intertwined mechanisms: by making the recipient ‘feel right’ during the message reception, by increasing the recipient’s strength of engagement with the message, which contributes to processing fluency, and by influencing elaboration likelihood (Cesario et al., 2008).

What psychological characteristics are most relevant in the context of CB? It seems that an individual’s morals play a significant role. For example, Smith and McSweeney (2007) and van der Linden (2011) showed that personal moral norms are one of the strongest predictors of CB. Furthermore, Aquino and Reed (2002) moral identity internalization, or degree to which moral traits are central to one’s self-concept, has been shown to influence: (a) type of charitable donations (time versus money), (b) donation intentions, (c) actual donations, and (d) emotions experienced during donations. Those who feel that morality is central to their self-concept: (a) prefer donating time instead of money, (b) show greater intentions to donate money, (c) are willing to actually donate more money, and (d) experience more positive donation related emotions than those who are lower on moral identity (Reed et al., 2007; Winterich et al., 2012). This evidence makes a strong case for the importance of individual morals in predicting CB.

Therefore, following from the RFT, it can be hypothesized that a person’s attitudes would change if a persuasive message was congruent with his/her moral views. One of the most influential and extensive theories that describe individuals’ moral systems is the Moral Foundations Theory (MFT; Haidt and Joseph, 2004; Haidt and Graham, 2007; Graham et al., 2011, 2012). MFT postulates that five different, innate, moral foundations provide a “first draft” of moral intuitions; but these intuitions can also be revised through exposure to social context and culture (for a detailed review, see Graham et al., 2012). The five moral foundations proposed by MFT are Care/Harm, Fairness/Cheating, Loyalty/Betrayal, Authority/Subversion, and Sanctity/Degradation (Graham et al., 2012). According to the theory, differences in these five foundations are responsible for differences in morality across individuals and cultures.

The first two foundations are called the *individualizing*
*foundations*, meaning that they emphasize inter-individual relations. Individuals scoring highly on these foundations are primarily sensitive to possible cruelty, unfairness, and inequality when making moral judgments (Graham et al., 2012). In contrast, the last three foundations are called the *binding foundations*, which bind individuals into communities. According to the MFT, those scoring highly on these foundations are primarily sensitive to social community, hierarchical relations, and physical and spiritual purity when making moral judgments. Graham et al. (2009) found that politically liberal individuals primarily endorsed and used individualizing moral foundations when making judgments (i.e., Care/Harm and Fairness/Cheating), whereas conservatives endorsed and used all five foundations more equally. These correlational patterns between morality and political ideology have been shown to be stable across cultures (e.g., Bobbio et al., 2011; Graham et al., 2011; Kosugi et al., 2014). This suggests at least two distinct, universal moral foundations profiles: a liberal and a conservative one.

Recent studies have examined the influence of (in)congruence of messages and individuals’ moral foundations on attitudes toward CB, charitable intentions and actual CB. For example, Feinberg and Willer (2013) showed that framing messages about the environment in terms of sanctity, rather than only care, shifted conservatives’ attitudes in a pro-environmental direction. Building on this, Wolsko et al. (2016) showed that the attitude change was also accompanied by increased donations to pro-environmental causes. Additionally, the congruence between individuals’ moral foundations and both the charity cause and persuasive calls-to-action has been shown to increase donation intentions and donations, but only for those individuals high on moral identity internalization (Winterich et al., 2012; Nilsson et al., 2016).

Despite this, previous studies have not explicitly contrasted charitable causes and calls-to-action in order to see, for example, whether congruent calls-to-action can have a positive impact on CB even if the charity cause is not in line with one’s moral foundations (e.g., conservatives donating to a charity supporting immigration). Therefore, studying attitudes and subsequent behavior change in response to the (in)congruence between persuasive appeals of differing charity causes and individuals’ moral foundations is a promising research avenue.

#### Changing Behavior by Changing Social Norms

In addition to changing attitudes toward CB, a fruitful approach may be to influence perceptions of social norms about CB. Social norms are the perceived rules of a community or group that dictate desired behavior (Kandori, 1992). Although some studies show that norms are the weakest of the TPB predictors (see Armitage and Conner, 2001), others have pointed out the need to distinguish between several types of norms before assessing their contribution to behaviors. Specifically, three distinct types of normative influences have been identified. First, norms can be *injunctive*, representing the information about what most others approve or disapprove. Second, norms can be *descriptive*, conveying information about what most others actually do (Cialdini et al., 1990). Finally, personal injunctive norms, or moral norms can be defined as *individual internalized moral rules* (Smith and McSweeney, 2007; van der Linden, 2011). Thus far, several studies have investigated the role of different types of norms on prosocial behavior, showing mixed results (e.g., Shang and Croson, 2009; van der Linden, 2011).

Several studies showed that moral and injunctive norms significantly predicted charitable intentions, after controlling for attitudes, perceived behavioral control and past behavior (Smith and McSweeney, 2007; van der Linden, 2011). However, in these studies, descriptive norms did not have a significant influence on charitable giving. In contrast, other studies have shown that descriptive norms can be significant determinants of CB and prosocial behavior in general. For example, Shang and Croson (2009) demonstrated that providing individuals with information about the amount of money that others donated, influenced the amounts donated in public radio fundraising, both immediately and in renewals the year after. Moreover, Croson et al. (2009) showed that the effect of providing social information in such a way on donations to public radio is fully mediated by changes in the perception of descriptive social norms. It is possible that these mixed findings are the result of differences in the saliency of norms that were used in those studies.

A norm must be salient to be efficient in changing behavior (Cialdini et al., 1990). This may explain why descriptive norms did not influence CB in some of the previous studies: CB is often performed privately (Smith and McSweeney, 2007). Because CB is often performed privately, individuals may not have an accurate sense of the extent to which other people engage in charitable action. In other words, descriptive norms may be ineffective in the context of individual CB because they are not salient enough. Therefore, providing explicit information about the behavior of others, and thus making descriptive norms about CB salient, is hypothesized to be a useful approach to changing perceptions about descriptive social norms, and consequently CB itself.

### Leveraging Social Networks to Foster Charitable Behavior

The percentage of CB conducted online grows every year (e.g., MacLaughlin, 2017). As such, it would be beneficial for charities to take advantage of this and make their online fundraising campaigns more efficient. For example, if charities could target interested potential donors more precisely and approach them with tailored, congruent calls-to-action, this could significantly improve their fundraising outcomes.

One way to target potential donors more precisely is by using big data produced by social networks. When browsing social networks and engaging in behaviors on those networks, people leave digital footprints. Previous research has shown that these footprints can be predictive of different psychological characteristics. Kosinski and his colleagues have conducted multiple studies exploring the potential uses of digital footprints created on social media sites to identify users’ psychological characteristics (e.g., Quercia et al., 2011; Kosinski et al., 2013, 2014; Youyou et al., 2015).^1^

Their research shows that it is possible to predict people’s personality trait scores (e.g., openness and extraversion) based on their digital footprints – specifically, Facebook *likes*. In fact, these predictions can be as accurate as those made by human judges, such as colleagues, friends or spouses (Youyou et al., 2015). Other researchers have demonstrated that it is possible to use social media data to predict various other characteristics. For example, Conover et al. (2011) demonstrated that people’s political alignment can be predicted from their Twitter data with 90.8% accuracy. Furthermore, since an individual’s different psychological properties are reflected in his/her digital footprints, it is possible that these footprints could be used to predict the individual’s moral foundations. If so, it would be possible for charities to directly target people who are more likely to support their cause and become donors, while avoiding those who are less likely to support that specific cause.

However, it has to be noted that the future of data collection and advertising on Facebook is questionable, both pragmatically and from an ethical standpoint. From a practical point of view, there are two limitations: declining use and more stringent data sharing policies. For example, a Pew Research Center^2^ study completed in 2018 found that Facebook is no longer the most popular online platform among teens, with only half of teens reporting using it. In addition, mostly due to the Cambridge Analytica scandal ^3^, Facebook has made it’s data sharing policies much more stringent. In practice, they currently do not allow new applications to collect users’ data for research purposes. Moreover, the scandal echoed extremely negatively among its users, decreasing users’ trust toward the company. For example, a survey from the Ponemon Institute (2018) found that between 2017 and 2018, the percentage of people who believed that Facebook was committed to privacy dropped by 52 percentage points. Therefore, users may be reluctant to give away their information, even for scientific purposes.

However, as will be described in the protocol, the collection of Facebook data and prediction of moral views from it is completely optional and constitutes the exploratory part of this protocol. It is perfectly possible to skip this part and follow only the confirmatory part of the protocol. This would significantly simplify the procedure, while still potentially providing theoretically and practically meaningful findings.

## Aims and Hypotheses

The project has five aims:

(i)to investigate the effect of morally (in)congruent calls-to-action and salient descriptive social norms on CB;(ii)to explore whether these effects occur when the charity’s cause is not aligned with a person’s moral profile;(iii)to examine whether the effects of (in)congruent calls-to-action are moderated by participants’ moral internalization scores;(iv)to investigate whether attitudes toward CB mediate the effect of (in)congruent calls-to-action on CB and whether descriptive social norms mediate the effect of normative information on CB;(v)to investigate whether individuals’ moral foundations can be predicted based on their Facebook behavior.

In previous studies, calls-to-action congruent with one’s moral foundations increased CB (Winterich et al., 2012). Therefore, we hypothesize that morally congruent calls-to-action will have a greater positive impact on CB compared with morally incongruent and neutral calls-to-action, regardless of whether the charity cause itself is in line with one’s moral foundations. Furthermore, we hypothesize that providing participants with normative information, thus making the descriptive norm salient, will significantly affect CB. Additionally, we expect that the impact of morally congruent calls-to-action will be greater in individuals with high moral internalization compared to individuals with low moral internalization. Also, in line with the assumptions of TPB (Ajzen, 1985, 1991), we expect that the effects of calls-to-action congruence on CB will be mediated by attitudes toward CB, and that the effect of normative information on CB will be mediated by the perception of descriptive social norms. Finally, although this part of the research would be purely exploratory, we expect to be able to predict some of the participants’ moral foundations by his/her Facebook behavior. The proposed effects are shown in the Figure 1.

**FIGURE 1 F1:**
[figure not shown]
Schematic representation of the proposed effects between (in)congruent calls-to-action, normative information, attitudes toward CB, descriptive social norms and CB.

## Materials and Equipment

### Participants

The number of participants needed when conducting the study according to this protocol mostly depends on the desired effect size we would like to be able to detect and the statistical power we would like to achieve. For example, using the multivariate analysis of variance, if we would like to achieve a power of at least 1−β = 0.90 to detect small effects (*f*^2^ = 0.02) with the probability of *Type I* error set at α = 0.05, we would need a sample size of *N* = 439 as calculated using *G^∗^Power 3* (Faul et al., 2007). However, given that it is expected that researchers will have to omit some participants whose scores do not meet the criteria for individualizing and binding groupings which will be determined from the data [due to calls-to-action not being (in)congruent enough with their moral views], it would be advisable to further increase the number of participants by 20%. Therefore, the ideal final sample would be around *N* = 527. Of course, if one would, for example, like to study the effects of (in)congruent calls-to-action and norms on donations to two different charity causes separately (e.g., those hypothesized to be more in line with liberals’ and conservatives’ values), one would need to double this number. On the other hand, if one is willing to the accept somewhat lower power of 1−β = 0.80, that is usually accepted in psychological research, one would need the sample size of *N* = 344, or around *N* = 412 if one decides to increase it by 20%.

The recruitment of participants can take place online. For example, in order to obtain a mixture of conservative and liberal participants, the link to the survey can be disseminated through different conservatively and liberally oriented Facebook groups (see Table A1 in Appendix A). Other online platforms where it is relatively easy to approach the users of different ideological positions can be also utilized, such as Reddit, Twitter etc.

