More importantly, however, we hope that the project will have useful practical implications. Specifically, we hope to be able to provide charities with some simple yet effective tools that they could utilize in subsequent fundraising campaigns. For example, charities will be able to benefit from the often easily attainable knowledge about the approximate ideological positions of their target group by changing the way in which they deliver information about their causes and frame donation pitches. In this way, they could decrease the risk of turning away people who would potentially become their donors, by addressing them the right way. Given the low implementation costs of these interventions, we believe that charities can significantly benefit from them even if the effect sizes are modest.

Looking at the previous literature, we can expect to find small to medium effect sizes of our interventions on donating behavior. For example, Winterich et al. (2012) found small to medium effect sizes for both charitable intentions and donations (Cohen’s *d* between 0.28 and 0.46). Croson et al. (2009) found a medium impact of descriptive social norms on donations to public radio’s (Cohen’s *d* = 0.58). However, we believe that, from the perspective of charity donations, even modest effects can have big practical importance. Statistically speaking, even if our interventions exhibit only small effects on CB (Cohen’s *d* = 0.2), this still means that 58% of donations from people from the *congruent appeal + norm* intervention will be higher than the mean donation from people from the *no intervention* condition. In case we find medium effects (*d* = 0.5), as much as 69% of the *intervention* donations will be higher than the mean of the *no intervention* donations (see http://rpsychologist.com/d3/cohend/ for the visualization and interpretation of Cohen’s *d* effect sizes). Thus, taking into account the relative ease and low cost of the implementation of these interventions, we believe that any kind of improvement in terms of donations can be considered as practically significant for charity organizations.

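### The stated 90% (80%) power at N = 439 (344) does not hold for the one-degree-of-freedom norm test, which has about 76% (64%) at the same effect size

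*Protocol article*

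**What the plan says.** The Participants section gives a worked sample size. It proceeds "using the multivariate analysis of variance", aims to "achieve a power of at least 1−β = 0.90" and "to detect small effects (*f*^2^ = 0.02", "with the probability of *Type I* error set at α = 0.05". The result is that "we would need a sample size of *N* = 439 as calculated using" G*Power, raised by 20% to about 527 because some participants are expected to be omitted when their moral profile fits neither group. For readers willing to "accept somewhat lower power of 1−β = 0.80", it gives 344, or about 412 after the same increase. The paragraph does not say which effect, how many degrees of freedom or how many outcomes were entered.

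The Stepwise Procedure section sets a 3 × 2 between-subjects design. The Statistical Analysis section puts two outcomes, time and money donated, into one MANOVA. That MANOVA tests the call-to-action, the norm, their interaction, and moderation of the call effect by moral internalization. The norm effect is a hypothesis in its own right under Aims and Hypotheses: "providing participants with normative information, thus making the descriptive norm salient, will significantly affect CB".

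**The concern.** In a MANOVA, a given f² does not fix one sample size for all tests. The noncentrality also depends on s, the smaller of the number of outcomes and the effect's degrees of freedom. With two outcomes, a 1-df effect has s = 1 and a 2-df effect has s = 2, so at the same f² and N the 1-df effect has half the noncentrality. A single N quoted for small effects in general therefore cannot carry the same power for the norm test as for the call-to-action tests.

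The article is written for other researchers to reuse. Its introduction describes mixed evidence on descriptive norms, so a null norm result is a real possibility. A reader relying on the Participants section would take that null as coming from a test with 90% power at f² = 0.02, when the type II error is about 24%, not 10%.

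**Working it through.** **Inputs.** From Participants: f² = 0.02, α = 0.05, target power 0.90 or 0.80, N = 439 or 344. From Stepwise Procedure: k = 3 × 2 = 6 groups. From Statistical Analysis: p = 2 outcomes. Effect df (q): call 3 − 1 = 2; norm 2 − 1 = 1; call × norm 2 × 1 = 2; call × internalization (continuous score) 2. Assumption: f² is G*Power's f²(V), the Pillai version.

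**Formula (Pillai F approximation).** s = min(p, q); df1 = p·q; df2 = s(N − k − p + s); λ = N·s·f². Power = P[F′(df1, df2, λ) > F(0.95; df1, df2)], where F′ is noncentral F.

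**Reproducing the article's figures.** Take p = 2, q = 3, so s = 2 and df1 = 6.
- N = 439: df2 = 2(439 − 6 − 2 + 2) = 866; λ = 439 × 2 × 0.02 = 17.56; power 0.900.
- N = 344: df2 = 2(344 − 6) = 676; λ = 13.76; power 0.800.

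These are the smallest Ns that reach 0.90 and 0.80, so both figures match exactly. With two outcomes, no other effect df gave this pair. Three outcomes with a 2-df effect (again s = 2, df1 = 6) also give exactly 439 and 344. The close match to both figures supports the f²(V) assumption.

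**Norm test.** Take p = 2, q = 1, so s = 1 and df1 = 2.
- N = 439: df2 = 439 − 6 − 2 + 1 = 432; λ = 439 × 1 × 0.02 = 8.78; power 0.757.
- N = 344: df2 = 337; λ = 6.88; power 0.643.

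**All planned effects at f² = 0.02, with the 3-df row for reference:**

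| Effect df (2 outcomes) | Planned test | Power at 439 | Power at 344 | N for 90% | N for 80% |
|---|---|---|---|---|---|
| 1 | Norm | 75.7% | 64.3% | 636 | 485 |
| 2 | Call; call × norm; call × internalization | 93.6% | 85.7% | 388 | 301 |
| 3 | None | 90.0% | 80.0% | 439 | 344 |

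For the norm test, 439 is 636 − 439 = 197 short, and 344 is 485 − 344 = 141 short.

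**Does the 20% increase cover the gap?** Suppose nobody were omitted. At N = 527, λ = 10.54 and norm power is 83.4%. At N = 412, λ = 8.24 and norm power is 72.8%. Both remain below 90% and 80%.

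**Detectable norm effect.** Solving for f² with q = 1 gives 0.029 for 90% power at N = 439 and 0.028 for 80% power at N = 344.

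**Sensitivity to the noncentrality convention.** With λ = df2·f² instead, norm power is 74.9% and 63.4%. The conclusion does not change.

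**The case against.** The Participants paragraph is offered as an example, says that N depends on the chosen effect size and power, and never assigns 90% to the norm test by name. The call-to-action, which the Pre-study section treats as the main independent variable, has more power than stated, as do the interaction and moderation tests. Among the planned effects the shortfall is confined to the norm test, and it concerns the small effect used for planning. The Significance of Research section cites d = 0.58 for descriptive norms. If that held on both outcomes, norm power at N = 439 would exceed 99% for an assumed outcome correlation of 0 to 0.5. All of this stands and lowers the severity. It does not make the figure right: the paragraph promises at least 90% for small effects, and a stated hypothesis tested in that MANOVA does not have it.

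Two stronger readings are tempting, and the documents support neither.
- A reader might infer that 439 can only have come from entering a 3-df effect. Three outcomes with a 2-df effect give the same pair, and the article lists attitudes and descriptive norms among its dependent variables. Two outcomes with 3 df fits the planned MANOVA better, but the input cannot be established.
- A reader might also set f² = 0.02 against the d = 0.2 in Significance of Research ("even if our interventions exhibit only small effects on CB") and conclude that the plan is underpowered for an effect it calls worthwhile. That d compares the combined congruent-plus-norm condition with no intervention, illustrates practical meaning and carries no power claim. Moreover, for the norm effect with d = 0.2 on both outcomes and no correlation between them, f² = 2 × 0.2² / 4 = 0.02, so the two definitions can coincide. Where they diverge depends on an outcome correlation that the article does not give.

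**Conclusion.** The point holds for the norm test. At f² = 0.02 its power is about 76% at N = 439 and 64% at N = 344, against the 90% and 80% stated. The 2-df tests have about 94% and 86%, so the quoted Ns match no single planned test of the two MANOVA outcomes. The result rests on f² being G*Power's f²(V), on six groups, and on the two outcomes named for the MANOVA; it needs no assumption about the correlation between them. It should be fixed, because a stated figure is wrong for one confirmatory hypothesis. It does not undermine the design or the call-to-action comparisons.

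**What to change.** In the Participants section, replace the single power statement with one for each effect, and give the effect df and number of outcomes entered:
- N = 439, f²(V) = 0.02, two outcomes: about 94% power for the 2-df effects (call-to-action, call × norm, call × internalization) and about 76% for the 1-df norm effect. The norm effect detectable with 90% power is f² of about 0.029.
- N = 344: about 86% and 64%. The norm effect detectable with 80% power is f² of about 0.028.

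Adding that the norm test would need 636 (90%) or 485 (80%) analysed participants at f² = 0.02, before any increase for omissions, lets those who reuse the protocol choose. The correction is a rewording and requires no extra enrolment. Its cost is a less favourable stated power for the norm hypothesis.
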